#### Phase 2 – structured semi-supervised ET following AC (week 13–26)

During phase 2, the same personalised, structured exercise program will be prescribed but with an increase in total exercise frequency to four sessions per week. To encourage increased independence there will be a reduced frequency of supervision (twice per week), with the remaining two sessions performed by the participants without supervision. Unsupervised sessions will be completed at each participant’s local health and fitness center or as a home-based exercise session depending on participant preference. During the supervised sessions, participants will receive feedback and guidance on structuring and performing their independent exercise sessions in order to increase their exercise self-efficacy. During phase 2, there will be an emphasis from AEPs on motivational interviewing and goal setting to assist participants in incorporating a regular exercise routine into their lifestyle and to assist in the transition to phase 3 of the exercise program. During week 5 and 10 of the phase 2 program, participants will have a de-loading week, which consists of a 10% reduction in aerobic exercise intensity and a reduction to 1 set of each resistance exercise, thereby facilitating an opportunity for recovery and adaptation.

##### Aerobic ET

During phase 2, participants will complete four sessions per week of aerobic training. The aerobic training program completed during phase 2 will consist of four session types: maximal steady state, endurance, interval and recovery sessions (outlined in Table 1 and Fig. 2) that alternate in a bi-weekly cycle similar to previous work in middle-aged adults shown to improve fitness and cardiovascular function [47]. In the first week, participants will complete two tempo sessions, one endurance session, and one interval session. In the alternate week, participants will complete one tempo, and two interval sessions that are interspersed with a recovery session. Tempo sessions will consist of 35 min at the %HRR corresponding to VT ± 10 beats/min as measured from the follow-up CPET at the 4-month testing visit. Endurance sessions will begin with 40-min at the %HHR 10–20 beats/min below VT, and progress by 5-min every fortnight until participants are completing a total duration of 60-min. The interval sessions will be identical to those completed at the end of Phase 1 of the program (4-min intervals at 85–95% HR_peak_). During weeks that incorporate two interval sessions, these sessions will be interspersed with a recovery session consisting of 30-min at an intensity 20–30 beats/min below %HRR at VT.

**Fig. 2 Fig2:**
[figure not shown]
Progression of aerobic exercise training volume during phase 2 of the exercise intervention. Participants complete four sessions per week consisting of a combination of tempo (blue), endurance (green), interval (red) and recovery sessions (yellow) which progress in volume each week over the 16-week training period. A de-load week (10% reduction in exercise intensity) is completed in weeks 5 and 10 to facilitate adaptation and recovery

##### Progressive resistance training

Participants will continue with the same PRT format of 2 sets of 6 exercises at 8–12 RM with 1–2 min rest between sets.

#### Phase 3 – step-down maintenance program (week 27–52)

During phase 3 of the exercise program, participants will continue to follow the same exercise program completed at the end of Phase 2, with adaptations from the study AEP so that they can complete the program independently at home and/or within their community health and fitness centre. Participants will be provided with ongoing support via weekly text reminders from the Physitrack mobile app, and six face-to-face review appointments with the study AEP. Review appointments will be used for goal setting, behavioural counselling and to progress the exercise program. The timeframe of the review sessions will be based on each participant’s preferences and the schedule of their other cancer treatments.

### Usual care group

Participants allocated to usual care will receive ongoing care from their oncology team but will not receive additional access to supervised exercise training from the research team. Control group participants will receive usual lifestyle advice as part of their routine clinical care in which patients will be provided a copy of the Cancer Council Australia booklet entitled “Exercise for People Living with Cancer.” Exercise will then be left to the patient’s volition, including any decision to enrol in a structured exercise program. A sham exercise comparator group will not be used because our primary outcome is an objective, measurable endpoint that is not subjected to patient expectancy or placebo effects.

### Measurements

All measures will be collected at baseline (within 2 weeks of the initiation of AC), following the completion of AC (4-months) and again at 12-months following the initiation of AC. Assessments will be performed at the Baker Heart and Diabetes Institute clinical research facility over two non-consecutive days. Testing session 1 will be conducted prior to chemotherapy, whilst it will be the aim to complete session 2 within the first 2 weeks of starting AC. Session 1 will consist of the resting echocardiography and blood pressure, cognition testing, questionnaires, CPET, blood sample, ExCMR and training in the use of the accelerometer devices for measurement of habitual physical activity. Tests completed during session 2 will include strength and physical function testing and dual-energy x-ray absorptiometry (DXA) scanning.

### Primary and secondary outcome measures

The primary outcome for this study will be the prevalence of functional disability (defined as VO_2_peak ≤ 18.0 mL/kg/min) measured via CPET at 12 months. The predictive ability of standard-of-care versus novel cardiac reserve measures will be addressed by comparing LVEF assessed via 3-dimensional (3D) echocardiography to cardiac reserve assessed via exCMR. For the purposes of this study, impaired cardiac reserve will be defined as a < two-fold increase in Qc from rest to peak exercise [33]. Impaired LVEF will be defined as a LVEF < 53% which is in line with current cardio-oncology guidelines [14, 15, 17].

Secondary outcomes will include changes in cardiopulmonary fitness and cardiac reserve, along with indices of resting cardiac structure and function, vascular stiffness, biochemical and blood-based markers of cardiovascular function, total- and regional body composition, bone mineral density of the lumbar spine and femoral neck, muscle strength, physical function, habitual physical activity, cognitive function, and multidimensional quality of life.

Additional exploratory outcomes will include the association between changes in cardiopulmonary fitness with indices of cardiac (cardiac reserve) versus non-cardiac factors (central vascular stiffness, haemoglobin concentration, lower body lean body mass, skeletal muscle composition of the thigh). The study will also explore the effect of the intervention on treatment-related variables including the dose of treatment received and response to neoadjuvant therapy.

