Findings from a meta-analysis indicated that time since treatment is an important risk factor for cardiotoxicity [13]. Indeed, the discrepancy between the rates of cardiac dysfunction detected soon after treatment and long-term heart failure incidence [10] highlights that an absence of measurable cardiac dysfunction soon after treatment does not adequately predict the risk of subsequent toxicity. This also emphasises the need for improved early detection strategies [14, 15]. Currently, the cornerstone for detecting AC-induced cardiac dysfunction is measuring changes in resting left-ventricular ejection fraction (LVEF) [14–17]. Whilst LVEF has been in use for decades, its ability to predict subsequent cardiotoxicity is limited by poor reproducibility [18, 19], load and heart rate dependence, and the current LVEF-based classification for cardiotoxicity (typically a > 10% drop from baseline to a value < 50–53%) shows weak associations with heart failure outcomes [20, 21]. Furthermore, half of HF patients have preserved LVEF (> 50%), highlighting that LVEF is insensitive to clinically significant cardiac dysfunction [22]. Consequently, there is growing interest in alternative measures for early detection of cardiac dysfunction following AC [15, 16].

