To compare the current standard-of-care (resting LVEF) to measures of cardiac reserve (peak exercise cardiac output; Qc) as predictors of functional disabilityTo determine whether a 12-month structured exercise training (ET) program reduces the proportion of BCa patients who are functionally disabled 12-months after the initiation of AC.

We hypothesize that:
Cardiac reserve will be superior to resting LVEF at predicting the development of functional disability 12-months following ACParticipating in a 12-month structured ET will reduce the proportion of patients who are functionally disabled 12-months following AC.

Secondary aims include assessing the effect of ET on changes in cardiopulmonary fitness and cardiac reserve, along with indices of resting cardiac structure and function, vascular stiffness, biochemical and blood-based markers of cardiovascular function, total- and regional body composition, bone mineral density of the lumbar spine and femoral neck, muscle strength, physical function, habitual physical activity, cognitive function, and multidimensional quality of life.

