### Cardiac structure and function

#### Echocardiography

Resting RV and LV function will be assessed by a comprehensive resting echocardiogram (Vivid E95, General Electric Medical Systems, Milwaukee, Wisconsin) with images analysed using offline analysis software (Echopac v13.0.00, GE, Norway). Resting echocardiography represents the current clinical standard of care to which exCMR will be compared [15]. LVEF will be used as the primary ‘standard of care’ measurement, and will be quantified from a full-volume 3D dataset according to standard recommendations. Additional measurements performed will include Doppler, torsion, global longitudinal strain and strain rate measurements.

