#### Cardiac magnetic resonance imaging

In addition to resting echocardiography, resting CMR (using the same protocol as described previously) [52] will be used to provide a highly accurate and comprehensive characterisation of resting cardiac structure and function. Breath-hold steady-state free precession (SSFP) sequences will be used for the quantification of ventricular volumes ventricular function and cardiac mass, whilst non-contrast T1 mapping will be used for myocardial tissue characterisation.

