The second primary aim of the study is to compare the predictive ability of standard-of-care measures (LVEF) with peak Qc measured by ExCMR in identifying women who will meet criteria for functional disability at 12 months. A multivariate regression will be used with five variables entered (age, LVEF, GLS, study group and peak Qc). The analysis will be stratified for group allocation (usual care vs exercise training) to account for the potential influence of the exercise intervention on the incidence of functional disability at 12-months. The sample size estimated for such an analysis can be calculated as 90 women (50 + 8 x no. of variables) using the method suggested by Green [74].

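### Aim 2 changes imaging modality and physiological state together, so a win for exCMR Qc supports 'exCMR versus resting echo' but not, by itself, 'reserve is superior to resting LVEF'

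*Protocol article*

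**What the plan says.** **Comparison.** The outcome section defines the Aim 2 contrast as "comparing LVEF assessed via 3-dimensional (3D) echocardiography to cardiac reserve assessed via exCMR". The Echocardiography section says that LVEF "will be quantified from a full-volume 3D dataset according to standard recommendations" and gives the reason: "Resting echocardiography represents the current clinical standard of care to which exCMR will be compared". The Abstract names both instruments in the aim, and Study design also sets ExCMR against resting echocardiography.

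**Hypothesis.** The Background does not name the instruments: "Cardiac reserve will be superior to resting LVEF at predicting the development of functional disability". The Discussion argues physiologically that current surveillance tells little about reserve because rest puts little stress on the heart.

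**Model.** The sample size section has "five variables entered (age, LVEF, GLS, study group and peak Qc". Read with the outcome and Echocardiography sections, this LVEF is the echo value.

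**Also collected.** Resting breath-hold CMR "will be used to provide a highly accurate and comprehensive characterisation of resting cardiac structure and function"; its sequences "will be used for the quantification of ventricular volumes ventricular function and cardiac mass". The Cardiac reserve section adds LVEF at rest and at each exercise stage of the exCMR series. The Measurements section plans all measures at every visit and puts echo and exCMR in the same testing session. Women with a CMR contraindication are excluded.

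**Precision.** Of LVEF the Background says that "its ability to predict subsequent cardiotoxicity is limited by poor reproducibility". The Cardiac reserve section reports an interstudy R of 0.98 for Qc. No reliability figure is given for LVEF by 3D echo or by CMR.

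**The concern.** Between the two predictors, the physiological state (rest or exercise) and the imaging modality (echo or CMR) both change. Random measurement error weakens the observed association of a predictor with the outcome. If echo LVEF is noisier than CMR Qc, LVEF can lose even when resting function is truly as informative as reserve.

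At stake is how a win for Qc is read. It would support exCMR over resting echo as practised. It would not show whether exercise is needed, or whether a resting CMR would have done as well. The Discussion hopes to inform clinicians about the utility of exercise-based assessment, so that distinction matters. The data to examine it are already planned for every participant, but the article names no CMR resting measure in the Aim 2 model.

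**Working it through.** **1. The plan's own figure.** Five variables under the stated rule: 50 + 8 × 5 = 90 women. With 10% attrition, 90 / 0.90 = 100. Both match the protocol, and the sample size is not in question here.

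**2. What differs between the predictors.**

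| Comparison | State | Modality | Quantity |
|---|---|---|---|
| Echo LVEF vs exCMR Qc (planned) | differs | differs | differs |
| Resting CMR LVEF vs exCMR Qc | differs | same | differs |
| Resting Qc vs high-intensity Qc, exCMR series | differs | same | same |
| Resting LVEF vs high-intensity LVEF, exCMR series | differs | same | same |

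Only the last two rows vary the state alone.

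**3. Direction of the measurement-error effect.** Let observed = √r × true + √(1 − r) × noise, where r is reliability. The association per observed SD then shrinks by roughly √r. For Qc, reading R = 0.98 as a reliability, √0.98 = 0.99. For echo LVEF (r assumed): √0.90 = 0.95, √0.75 = 0.87, √0.60 = 0.77.

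**4. Size, by simulation.** From the protocol: n = 90, 24% events (0.24 × 90 ≈ 22) and R = 0.98 for Qc. Assumed: equal true log odds ratios per SD for the two traits, their correlation, and the LVEF reliability. With equal precision Qc should have the higher AUC in 50% of trials.

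Setting A (correlation 0; log odds ratio 0.5 or 0.8; 3,000 replicates):

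| LVEF reliability | Mean AUC gap favouring Qc | Qc has higher AUC |
|---|---|---|
| 0.90 | 0.003–0.004 | 51% |
| 0.75 | 0.015–0.025 | 56–60% |
| 0.60 | 0.025–0.039 | 60–65% |

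Setting B (correlation 0.3; log odds ratio 0.7 or 1.0; 4,000 replicates):

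| LVEF reliability | AUC gap favouring Qc | Qc has higher AUC |
|---|---|---|
| 0.98 | −0.003 to 0.004 | 50–51% |
| 0.90 | 0.009–0.012 | 54–56% |
| 0.80 | 0.017–0.025 | 59–61% |
| 0.70 | 0.035–0.042 | 65–68% |
| 0.60 | 0.043–0.058 | 72–75% |
| 0.50 | 0.061–0.076 | 76–82% |

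The row at 0.98 shows simulation noise of about 0.004 in the AUC gap.

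**5. Significant false wins.** Ranking first is not a claim of superiority. With a paired DeLong test (22 events, log odds ratio 0.5 or 0.8, correlation 0 or 0.3, 4,000 replicates), Qc wins significantly in 2.6–2.9% of trials when both reliabilities are 0.98. The figure is 2.9–4.0% at LVEF reliability 0.90, 4.7–6.4% at 0.75 and 5.0–9.2% at 0.60.

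**6. Room for a further model.** Replacing echo LVEF by resting CMR LVEF keeps five variables and 90 women. Adding it as a sixth gives 50 + 8 × 6 = 98, above the 90 expected after attrition. Replacement is the version that fits.

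**The case against.** **The comparison is of two strategies and is declared as such.** The Abstract, Study design and Echocardiography section all name the instruments, and echo is chosen because it is current practice. In a strategy comparison the instrument, with its imprecision, belongs to the strategy. The Background even lists poor reproducibility among the reasons for looking beyond LVEF. This stands. A reader might infer that the Aim 2 comparison is invalid; the documents do not support that. Only the step from it to the wider hypothesis is open.

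**The size is assumed.** The Background remark concerns LVEF in general, not 3D echo. The R of 0.98 is for Qc, so CMR LVEF need not be as reliable. The simulations use single-predictor AUCs, whereas the plan is a five-variable regression. This also stands: a reader might infer that a Qc win would be mostly artefact, but the figures do not show that.

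**Swapping in CMR LVEF does not isolate exercise.** It still sets a resting ratio against an exercise flow, and the breath-hold and real-time techniques differ. This stands, and it is why a same-quantity contrast within the exCMR series is preferable as an addition.

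**Supportive models are commonly left to the analysis plan.** True, and the absence of such a model from a condensed article is not in itself an error. What remains is that the hypothesis, as stated in the article, is wider than the comparison stated there.

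**Conclusion.** The point holds in a limited form. Echo LVEF versus exCMR Qc is a sound main analysis of two strategies. Because modality and state change together, a Qc win alone does not establish that reserve is superior to resting LVEF, as the Background hypothesis puts it and the Discussion's low-stress argument suggests. That confounding follows from the design and needs no reliability figure.

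How much it favours Qc is unknown. If echo reliability is 0.9 or more, the advantage is small: an AUC gap of about 0.01 or less and a higher Qc AUC in 51–56% of trials. At 0.60 the gap is 0.025–0.058, with Qc ahead in 60–75%. Even there, a significant false win stays below 10% in the settings tried. These figures rest on equally predictive true traits, R = 0.98 read as a reliability, and assumed effect sizes and correlations.

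Priority: worth considering. It is an inexpensive gain in interpretability and not a flaw that undermines Aim 2.

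**What to change.** Keep 3D-echo LVEF versus exCMR Qc as the main Aim 2 analysis. In the paragraph on the second primary aim, pre-specify:

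1. A supportive model in which resting CMR LVEF replaces echo LVEF: same women, same visit, still five variables.
2. Ideally, a same-quantity contrast from the exCMR series: resting Qc against high-intensity Qc, or resting against high-intensity LVEF.
3. A rule for the conclusion: state that reserve is superior to resting function only if Qc also outperforms these CMR resting measures. Otherwise limit the conclusion to exCMR versus resting echocardiography.

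The cost is one or two extra models on data already planned, with no new scans or participants, and a stricter condition for the wider claim. CMR LVEF may not match Qc in precision, so the supportive model reduces the ambiguity without removing it.

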### Cardiopulmonary fitness and functional disability

Cardiopulmonary exercise testing will be used to assess VO_2_peak and functional disability. VO_2_peak, VT and ventilatory efficiency (Minute ventilation to carbon dioxide production slope [VE/VCO_2_ slope]) will be assessed using a continuous ramp protocol on an electronically braked upright cycle ergometer (Lode Excalibur Sport, Lode BV Medical Technology, Groningen, NL) with breath-by-breath expired gas analysis (Vyntus™ CPX, CareFusion, San Diego, CA) in accordance with published guidelines [48]. A flow meter and gas analyser calibration will be performed prior to each test in accordance with the manufacturer guidelines. Two minutes of resting data will be collected prior to the start of exercise, after which participants will undertake a one-minute warm-up at 10–25 W. The workload then increases at a continuous rate of 5–25 W/min until volitional fatigue or symptom limitation. The protocol will be individualised based on each participant’s self-reported physical activity levels, with the aim of reaching volitional exhaustion by 8–12 min. HR and rhythm will be monitored continuously throughout exercise using a 12-lead ECG (Vyntus™ CPX, CareFusion, San Diego, CA) and blood pressure (BP) will be measured every 2 min using an automated cuff (Tango® M2 ECG-gated Automated Blood Pressure Monitor, SunTech Medical Inc., Morrisville, NC). For the purposes of analysis, the test will be considered a peak effort if two of the following criteria are reached: 1) volitional exhaustion; 2) a respiratory exchange ratio > 1.1, and/or 3) > 85% of age-predicted maximal HR [48]. VO_2_peak is defined as the highest 30-s rolling average calculated from six consecutive 5-s VO_2_ epochs. Functional disability will be defined as a VO_2_peak ≤ 18.0 mL/kg/min ref. VT will be assessed using the V-slope method, and the relative proportion of VO_2_peak at which the VT occurs will be used as a measure of changes in submaximal exercise capacity. VE/VCO_2_ slope will be obtained from linear regression analysis of minute ventilation (VE) and expired carbon dioxide (VCO_2_) from the end of the warm-up to the VT [48]. HR and blood pressure (BP) recovery will also be assessed at 1, 2 and 4 min after the end of the test as markers of autonomic function.

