Current approaches for preventing cardiovascular morbidity in patients receiving anthracyclines include treatment withdrawal and/or modification, and pharmacological strategies. Treatment withdrawal prevents further cardiac injury, however is problematic due to the potential negative effects on cancer-related outcomes [34]. The use of pharmacotherapies such as Dexrazoxane [35, 36], angiotensin converting enzyme inhibitors [35], and beta-blockers [35] can reduce the risk of subsequent cardiac dysfunction. However, this appears at odds with the current trend towards personalized therapy, given that this would result in the majority of patients being treated unnecessarily. Additionally, given cardiac function is unlikely to be the sole driver behind AC-induced impairments in exercise capacity and functional disability [37], the ability of cardiac-focused pharmacotherapy to completely reverse a patient’s exercise intolerance may be limited. Exercise training (ET) has emerged as an important therapeutic tool for addressing a number of adverse effects associated with cancer treatment [38], and there is growing interest in its use for preventing cardiotoxicity and functional disability [39]. However, whilst exercise can prevent or attenuate declines in VO_2_peak during BCa chemotherapy (predominantly anthracycline-based) [38, 40–42], no randomised trials have investigated whether it can reduce the incidence of important clinical endpoints such as functional disability. Furthermore, the degree to which the beneficial effects on VO_2_peak reflects cardiac versus peripheral ‘protection’ is still unknown and will have important implications for the cardioprotective role of exercise. The primary trials investigating the effect of exercise training on cardiac function during AC have shown neither a beneficial, nor detrimental effect on cardiac function [32, 40, 43]. These studies have been small, short-term and the majority have relied on resting measurements of cardiac function to identify cardiac dysfunction. Thus, there is a need for larger, longer RCTs that are based on outcomes that are more sensitive to cardiac dysfunction and prognosis.

Therefore, in women with BCa undergoing anthracycline-based chemotherapy, this 12-month RCT has two primary aims:

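### VT as a proportion of VO2peak is a poor measure of change in submaximal capacity, because exercise is expected to change the denominator

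*Protocol article*

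**What the plan says.** In the protocol article, the section on cardiopulmonary fitness and functional disability lists "VO_2_peak, VT and ventilatory efficiency" among the variables taken from the exercise test. It then gives the method for each:

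- **Numerator.** "VT will be assessed using the V-slope method".
- **Denominator.** "VO_2_peak is defined as the highest 30-s rolling average calculated from six consecutive 5-s VO_2_ epochs".
- **Use.** "the relative proportion of VO_2_peak at which the VT occurs will be used as a measure of changes in submaximal exercise capacity".

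That section gives no such role to absolute VO2 at VT or to work rate at VT. It also does not say whether a higher or a lower proportion counts as better.

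The outcomes section places fitness in the secondary tier: "Secondary outcomes will include changes in cardiopulmonary fitness and cardiac reserve". The Background states the expected effect on the denominator, namely that "exercise can prevent or attenuate declines in VO_2_peak during BCa chemotherapy".

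**The concern.** A measure of change in submaximal capacity should move when submaximal capacity moves, and in a known direction. A ratio to VO2peak does so only if VO2peak stays put or moves in the same way in both arms. Here the trial is built on the expectation that VO2peak will differ between the arms, and its primary outcome is a VO2peak threshold. The ratio therefore mixes the effect of exercise on VO2 at VT with its effect on VO2peak, and the second enters with a negative sign.

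At stake is the reading of one secondary result. Exercise could improve VO2 at VT, yet the between-arm comparison of the named measure could show no difference or point towards usual care.

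**Working it through.** The article states no figure for this measure, so there is nothing to reproduce. The check is algebra followed by an illustration.

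**Algebra.** Let R = VO2 at VT / VO2peak. Then log R = log(VO2 at VT) - log(VO2peak), and so

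effect on log R = effect on log(VO2 at VT) - effect on log(VO2peak).

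Suppose exercise benefits both quantities relative to usual care, and a higher R is read as better. Then:

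1. Equal proportional benefit: R shows no effect.
2. Larger proportional benefit on VO2peak: R favours usual care.
3. Larger proportional benefit on VO2 at VT: R favours exercise, in agreement with absolute VO2 at VT.

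**Assumed inputs.** The baseline is VO2 at VT 12 and VO2peak 20 mL/kg/min, so R = 12/20 = 60.0%. The percentage changes are also assumed. Only the 18.0 mL/kg/min threshold comes from the article.

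**Trained woman, both +10%.** 13.2/22 = 60.0%, a change of 0.0 points, although VO2 at VT rose by 1.2 mL/kg/min.

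**Control, VO2peak -15%.** 20 × 0.85 = 17.0, which is below the threshold. The change in VO2 at VT is varied:

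| Control VO2 at VT | Control R | Change in R (points) | R, trained minus control (points) | VO2 at VT, trained minus control (mL/kg/min) |
|---|---|---|---|---|
| -20%: 9.6 | 9.6/17 = 56.5% | -3.5 | +3.5 | 13.2 - 9.6 = +3.6 |
| -15%: 10.2 | 10.2/17 = 60.0% | 0.0 | 0.0 | 13.2 - 10.2 = +3.0 |
| -10%: 10.8 | 10.8/17 = 63.5% | +3.5 | -3.5 | 13.2 - 10.8 = +2.4 |
| unchanged: 12.0 | 12/17 = 70.6% | +10.6 | -10.6 | 13.2 - 12.0 = +1.2 |

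In every row absolute VO2 at VT favours exercise. R goes from favouring exercise, through zero, to favouring usual care.

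**Check of the third row against the identity.** The effect on VO2 at VT is ln(1.10/0.90) = 0.201. The effect on VO2peak is ln(1.10/0.85) = 0.258. The difference is -0.057, and exp(-0.057) = 0.944, which equals 60.0/63.5.

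**A trained woman who gains more at peak.** With VO2peak +15% (23.0) and VO2 at VT +10% (13.2), R = 13.2/23 = 57.4%, a fall of 2.6 points although both values rose.

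**Other baselines.** For the control with VO2peak -15% and VO2 at VT -10%, baselines of 11/20 and 13/22 give +3.2 and +3.5 points. The trained woman with both +10% again scores 0.0.

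**The case against.** The strongest reply is that the direction of the error depends on assumed numbers. The article supports different VO2peak movement by arm but says nothing about how VT will move. Much of the training is prescribed relative to VT, so a larger proportional response at VT than at peak cannot be excluded. Take a baseline of 12/22 = 54.5%. If usual care goes to 9.5/18 = 52.8% and exercise to 14/24 = 58.3%, the ratio favours exercise by 5.6 points, the same direction as absolute VO2 at VT. This stands, and it limits the point: the ratio can mislead, but need not.

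Four further points bear on what a reader might infer.

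- *That the ratio rises whenever VO2peak falls, or simply reverses the arm effect on VO2peak.* It does not. It rises only if VO2 at VT falls proportionately less than VO2peak. The first two rows of the table show a fall and no change.
- *That the article scores a rise as improvement.* It sets no direction. The lack of a fixed good direction is part of the problem, but labels such as improved or unchanged would be the reader's own.
- *That absolute VO2 at VT is unavailable.* It is not. VT is among the listed variables, the ratio is called only one measure of submaximal change, and nothing prevents VO2 at VT from being reported. What the article does is name the ratio for this purpose and leave the absolute value without that role.
- *That the ratio defeats the purpose of a submaximal measure because it depends on peak effort.* A test stopped early, but after VT, does lower VO2peak and raise the ratio. However, the article does not give independence from effort as the reason for the measure. It sets peak-effort criteria, and it includes the VE/VCO2 slope, which is taken only up to VT and does not use VO2peak.

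**Conclusion.** The concern holds in a limited form. As an algebraic fact, the ratio shows whether VO2 at VT changed proportionately more than VO2peak, not whether submaximal capacity changed. In this trial the denominator is expected to differ by arm, so the distinction matters. In the illustration, with VO2peak down 15% in the control and both values up 10% in the trained woman, the between-arm difference in the ratio runs from 3.5 points for exercise to 10.6 points for usual care. Absolute VO2 at VT favours exercise by 1.2 to 3.6 mL/kg/min throughout. These sizes rest on assumed baselines and changes and on reading a higher ratio as better.

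The consequence is modest. One component of the secondary cardiopulmonary-fitness outcome is affected. A reader might infer that an adverse ratio would contradict the primary result. It would not, because the primary outcome is VO2peak against a threshold at 12 months, the ratio does not enter it, and VO2peak reported alongside would show why the ratio moved. The measure should still be corrected before the analysis, since a change made after results are known would look post hoc.

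**What to change.** In the section on cardiopulmonary fitness and functional disability, name absolute VO2 at VT as the measure of change in submaximal exercise capacity. Express it in mL/kg/min to match VO2peak and let that version govern. Give L/min as a supporting analysis, and keep VT as a percentage of VO2peak as a descriptive variable only.

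The cost is about one sentence. VO2 at VT is already needed to form the ratio, so there is no new test and no added burden on participants. There is a small downside: a value in mL/kg/min also moves with body mass, which cancels out of the ratio, and body mass may change over the 12 months. The L/min analysis is there to show whether that matters.
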